In addition to an adequate legislative framework, a preventive standpoint is essential which, with knowledge and sensitisation, will allow healthcare providers to approach the question of FGM and thereby avoid the conflicts brought about by legislation of aspects linked to the privacy and identity of the migrant persons.

Given the accessibility of the population to the universal healthcare available in Spain, primary healthcare may have a key role in the prevention of FGM [24,25], with these professionals being in the first line for dealing with this problem. Interdisciplinary teams with paediatricians, family physicians, nurse, social workers, gynaecologists and midwives, allow an integral approach to the families from the countries of sub-Saharan Africa where the question of FGM is always very present [26,27].

We are not aware of other previous experiences developed in primary healthcare in Spain or in Europe. Several studies have described registries of cases and others have reported knowledge, attitudes and practices related to FGM by professionals of specialised care [28], but to our knowledge there are no publications on these aspects in relation to first level healthcare or to preventive work undertaken from the primary care setting. We therefore developed the present study to provide knowledge and elements for improvement in the approach to FGM to prevent this problem on behalf of the healthcare professionals.

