#### Secondary objectives

4. Identify the training needs of the primary care professionals in relation to how to approach FGM.

5. Quantify the frequency of presentation of problems related to FGM in primary care offices.

6. Attempt to approach the position of the immigrant families given the intervention of healthcare agents to avoid these practices.

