## Methods/design

This is a transversal, descriptive study based on a survey regarding the knowledge, attitudes and practices (KAP) of the professionals, and users from countries of sub-Saharan Africa versus the performance of FGM. The study will be carried out in the 25 Primary Healthcare Centres from (PHC) Northern Barcelona and the Maresme Region (Barcelona, Spain) and from the counties of Girona (Girona, Spain) providing healthcare coverage to a population of 487,000 inhabitants.

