#### Selection of healthcare providers

The study includes all the professionals of the PHC teams, the Sexual and Reproductive Healthcare Programme and the Departments of Paediatrics and Gynaecology-Obstetrics of the hospital centres. It will also include the social workers linked to PHC. In the Catalonian Healthcare System, primary healthcare professionals work in teams who attend the healthcare needs of the population assigned in a determined territory. These teams are made up of family physicians, general medicine physicians, paediatricians, nurses and social workers. Support programs are available within the setting of sexual and reproductive health and these are mainly constituted by gynaecologists, nurses and midwives. All these healthcare providers will be asked to voluntarily and anonymously participate in filling out the questionnaire.

The target population will therefore be all the healthcare providers of the previously mentioned groups and teams who will be contacted through the heads of the teams and informative sessions in each of the centres and departments. A response rate of around 75% has been estimated, similar to that obtained by the same system in a previous study by our group in 2001 and 2004 [14,15].

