### Study variables

The questionnaire to the healthcare professionals will assess knowledge on FGM, attitudes and skills in approaching this problem in relation to the following areas:

• Sociodemographic data and of the professional setting: age, gender, professional category, work centre or department.

• Assessment of knowledge on: typology of FGM, cultural origin, geographic distribution and ethnicity of FGM, legal implications, consequences for the health of the women, formation received.

• Assessment of the attitudes of the professionals in relation to: beliefs regarding FGM, professional interest in relation to FGM, convenience or need to act on this problem, fears or insecurity generated on considering this subject, availability of preventive interventions, negativity towards immigrant patients, attitude toward judicial interventions related to FGM and their implications.

• Agreement or disagreement of the professional towards the response or actions to be undertaken in a situation of risk for a girl or towards a recent FGM.

• Previous contact with cases of FGM or situations of risk and previous experiences.

Similarly, the questionnaire for the families will include the following areas:

• Sociodemographic data: age, gender, country of origin, ethnicity, years of residence in Spain, number of children. Position of the different members of the family towards FGM.

• Knowledge of the consequences which FGM may have on the health of a girl.

• Knowledge of Spanish legislation and of the country of origin regarding FGM and the consequences of its practice, experiences (acceptation or rejection) related to the criminalisation of this practice.

• Position (acceptation or rejection) towards a possible preventive action on behalf of the healthcare professionals in Spain.

• Expectations towards the proposal of a preventive intervention aimed at their communities of origin, consequences of not performing FGM in relation to the community in both the country of origin and destination (diaspora), acceptation of alternative rituals to FGM.

Sociodemographic data (age, gender, ethnicity, country of origin, years of residence in Spain and number of children) will be collected from the sub-Saharan healthcare users who do not wish to complete the questionnaire, with the aim of detecting possible differences between users who accept and refuse to participate in the study.

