### Analysis plan

The quality of the data will be evaluated, treating extreme and rare values. Regarding the questionnaire to the healthcare professionals, to answer the first and second objective, each of the issues included in the area of assessment of knowledge (typology of FGM, cultural origin, geographic distribution and ethnicity of FGM, legal implications, consequences for de health of the women and formation recived) and included in the area of assessment of the attitudes of the professionals (beliefs regarding FGM, professional interest in relation to FGM, convenience or need to act on this problem, fears or insecurity generated on considering this subject, availability of preventive interventions, negativity towards immigrant patients, attitude toward judicial interventions related to FGM and their implications) will be described for univariate analysis, mean and standard deviation for quantitative variables and frequency and percentage for qualitative variables. Then a bivariate analysis will be performed between each of the above issues and gender of the healthcare professionals, age, professional category and work centre or department. To do this we will use different tests adequate to the type of data. To answer the third objective, we will do the same as the first and second objective but with each of the issues in the area of agreement or disagreement of the professional towards the response or actions to be undertaken in a situation of risk for a girl or towards a recent FGM. To quantify the frequency of presentation of problems related to FGM in primary care offices (fifth objective), we will do the same as first, second and third objectives but with each of the topics in the area of previous contact with cases of FGM or situations of risk and previous experiences. By analyzing all this information, and mainly from the results obtained with the area of assessment knowledge, we will be able to identify the training needs of the primary care professionals in relation to how to approach FGM, providing a good answer to the fourth objective. A multiple logistic regression model will be used to assess the characteristics of the professionals associated with correct identification of FGM (types that exist, countries in which it is performed, health consequences, reasons for implementation and prosecution by law). Regarding the questionnaire for the families, to describe the sample of immigrant families, each of the issues of the areas of the study will be described for univariate analysis, mean and standard deviation for quantitative variables and frequency and percentage for qualitative variables. To answer the last objective (sixth objective), bivariate analysis will be performed between the area of sociodemographic data and the remaining areas of study to evaluate possible differences between men and women, young persons and the elderly, based on the country of origin, ethnicity, years of residence in Spain and the number of children, with regard to knowledge of the consequences on health which FGM may imply, knowledge of legislation, position towards a possible preventive action on behalf of the healthcare professionals, expectations towards the proposal of a preventive intervention aimed at their communities of origin, consequences of not performing FGM in relation to the community in both the country of origin and destination, and acceptation of alternative rituals to FGM. Comparison between responders and non-responders immigrants will be performed using bivariate analysis to evaluate possible differences in participation between men and women, young and the elderly, based on the country of origin, ethnicity, years of residence in Spain and based on the person who proposed their participation in the study. This will be performed with tests according to the type of distribution and type of variables. Moreover, a multiple logistic regression model will be used to assess the characteristics associated with a possible preventive acceptance by immigrant families. The criterion of statistical significance will be p < 0.05.

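### Objective 5 promises how often FGM-related problems present in primary care, but the planned analysis describes only what professionals report of their previous contact

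*Protocol article*

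**What the plan says.** Under Secondary objectives, the fifth aim is to "Quantify the frequency of presentation of problems related to FGM in primary care offices". The only matching data named under Study variables are "Previous contact with cases of FGM or situations of risk and previous experiences", collected from professionals.

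The Analysis plan treats this objective as it treats the first three: "we will do the same as first, second and third objectives but with each of the topics in the area of previous contact". The summaries carried over are "mean and standard deviation for quantitative variables and frequency and percentage for qualitative variables", followed by bivariate comparisons by gender, age, professional category and work centre or department.

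On design, the article states: "This is a transversal, descriptive study based on a survey regarding the knowledge, attitudes and practices (KAP) of the professionals". No register or visit data are described. On respondents, Selection of healthcare providers states: "The study includes all the professionals of the PHC teams, the Sexual and Reproductive Healthcare Programme and the Departments of Paediatrics and Gynaecology-Obstetrics of the"; the sentence ends by placing these departments in hospitals. Under Data collection, forms are anonymous and carry only a team code.

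**The concern.** A frequency of presentation needs presentations in the numerator, and a period or a denominator of patients, visits or office time. The planned analysis has professionals as its units and their reported past contact as its variable. If the resulting percentage is published as the answer to objective 5, readers may take it as a measure of how often the problem reaches primary care. The Discussion intends the results to inform training strategies and guidelines, so the misreading could carry into planning.

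A second issue lies within the comparisons. Contact at any time in the past accumulates with years of exposure. A difference between age groups or professional categories may then reflect a longer look-back and not a higher rate of encounter.

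**Working it through.** The article gives no target figure for objective 5, so there is nothing to reproduce. Its only sample size, 191, belongs to the migrant sub-study and does not bear on this point.

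**1. Promised quantity against planned quantity**

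| | Objective 5 as worded | Analysis as planned |
|---|---|---|
| Unit | a presentation | a responding professional |
| Denominator | patients, visits or time | respondents |
| Setting | primary care offices | primary care teams, the reproductive health programme and hospital departments |
| Result | a frequency of presentation | a percentage of professionals, or a mean per professional |

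The two columns differ in every row. A recall period in the questionnaire would bound the time but would leave the unit and the setting as they are.

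**2. What a percentage with past contact can say about a rate (illustration)**

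Inputs: in the earlier survey described in the Background, 21% of reproductive-health staff had detected or known of a case, with no period given in the article. The earlier work is dated 2001 and 2004 (Selection of healthcare providers). The first cases detected in Spain are dated 1993 (Background). Assumptions: a constant annual chance *a* of contact, and a look-back of *T* years starting in 1993.

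Formula: s = 1 − (1 − a)^T, so a = 1 − (1 − s)^(1/T), with s = 0.21.

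- T = 1: a = 21%
- T = 2001 − 1993 = 8: a = 1 − 0.79^(1/8) = 2.9%
- T = 2004 − 1993 = 11: a = 1 − 0.79^(1/11) = 2.1%

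Ratios: 21/2.9 ≈ 7 and 21/2.1 = 10. The same percentage fits annual chances that differ 7- to 10-fold, depending on the look-back.

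**3. Effect on the planned comparisons (same formula)**

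Take two groups with the same annual chance of 2.9%. After one year of exposure 2.9% report contact; after eight years 1 − (1 − 0.029)^8 ≈ 21% do. A comparison of contact at any time would show a large difference where the rate of encounter is equal. Study variables lists age, gender, category and work centre, but not years in practice, so age is the only available proxy for exposure.

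**4. If a number of cases is asked**

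The article says that "primary healthcare professionals work in teams who attend the healthcare needs of the population assigned in a determined territory", and all team members are invited. Two colleagues who know the same family can each report it. The forms carry a team code and no case identifier, and no step to remove duplicates is described. A mean or sum of reported cases would then exceed the number of distinct cases by a factor equal to the average number of colleagues reporting each case. The article gives no value for that factor, so no size is put on it here.

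**The case against.** The strongest reply is that the questionnaire is not shown and is still to be developed through a nominal group, a pilot and a revision (Questionnaire elaboration). It may set a recall period or ask for a number of cases. The Analysis plan allows means for quantitative items, so the result need not be a bare percentage. This stands. A reader might infer that the instrument has no time window, or that it yields only a share of staff with any contact. The article supports neither inference. It supports only that no period is stated and that the analysis is per respondent.

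The reply on duplicates also stands in part. A reader might infer that shared cases inflate the result several-fold. The plan never proposes to add reports into a case total, and a share of professionals is valid as a share even when colleagues know the same family. The Background line that "Interdisciplinary teams with paediatricians, family physicians, nurse, social workers, gynaecologists and midwives, allow an integral approach to the families" describes teamwork. It does not say how many colleagues know each case. Duplication matters only for a case count.

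Finally, the plan already compares contact by age and category. That helps, but age is a rough proxy for exposure time. None of these replies supplies a denominator of presentations or confines the answers to primary care offices.

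**Conclusion.** The mismatch holds on the text, whatever the final item wording: the analysis fixed for objective 5 describes professionals' reported contact and cannot deliver a frequency of presentation in primary care. The consequence is moderate. The objective is secondary and descriptive, and the sample size does not rest on it, but it affects what the study can conclude.

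The 7- to 10-fold range is an illustration and not an error measured in this study. It assumes a constant annual chance of contact and a look-back that starts with the first detected cases in 1993. A reader might extend the look-back to a 20-year career and infer a wider range. That sits poorly with those dates, and the article gives no career lengths.

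**What to change.** Reword objective 5 as the proportion of professionals who report having encountered an FGM case or a girl at risk, ever and within a stated recent period, for example 12 months. Report it by professional category, with primary care separate from hospital departments. State in the plan and in the report that these are reports by professionals and not counts of distinct cases.

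Optionally, use the existing team code to report the proportion of teams with at least one report. That figure depends on team size and response rate and should be read with both.

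The cost is small: one added item or recall phrase in a questionnaire not yet final, a more modest objective, and no extra participants.

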### Data collection

The managing team of each centre or department will be contacted to introduce the study and its objectives. When the administration of the centre authorises participation in the study a member of the research team will go to each of the PHC to inform the professionals, motivate them and invite them to participate. The questionnaires will be given and collected in a specific session in each PHC. One person in each PHC will be responsible for the administration and collection of the questionnaires from the professionals who are absent on the day of the session to be thereafter sent to the research team within a maximum time of two weeks for later processing and analysis of the data collected. The questionnaire to the professionals will be anonymous and self-administered. It will only have a code indicative of the team to which the health professional belongs to obtain the rate of response from each centre. At no time will the data obtained be able to identify the responding professional. Neither will data processing and analysis be able to identify the centres since they will be indexed with an alpha-numerical code with no relationship to the geographic location or service providing entity.

To administer the questionnaires to the families, cultural mediators from the healthcare centres will collaborate. These mediators will introduce the interviewer and will accompany them throughout the whole process of completing the questionnaire to clarify any concept or doubt in relation to the same which may come up among the families surveyed. The participating mediators are experts with specific training in intercultural mediation. For this study they will be instructed as to the characteristics of the questionnaires and the objectives and methods of the study. They will be trained in giving the questionnaire and the objectives sought with each of the questions will be explained. The questionnaire will always be given under the supervision of a member of the investigative team. The questionnaire to the families will be anonymous but hetero-administered. Information regarding the families who refuse to participate in the survey will also be collected.

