A preventive interdisciplinary task which will allow the designing of strategies focused on the eradication of these practices and evaluation which allows knowledge of the cases produced and the resolution of conflicts considered in both Spain and Africa are therefore essential. Consciencious, reflexive and rigourous work of information, training and sensitisation are necessary. To do this, the proposal herein presented will provide better knowledge of the problem of FGM and how primary care professionals may approach this problem since there are no studies in Spain and very few in Europe. Training strategies and the development of guidelines may therefore be elaborated to enable primary care professionals to prevent and treat this new problem in the PHC.

On the other hand, it may be a model of positive intervention through transcultural care which is respectful of the values and beliefs of the people.

The main limitation of this study is the little collaboration received from the professionals at the time of performing the survey. To surpass this limitation, different researchers of the project will go to the primary healthcare centres to inform the professionals and increase their participation with distribution in a specific meeting with all the professionals of the PHC.

The presence of communities of sub-Saharan immigrants in our area is very concentrated in determined zones of each municipality thereby implying that the level of sensitisation for the problem of the study may vary greatly based on the demographic reality of each PHC. This concentration of immigrant communities in determined areas will not influence the results since our target population is all the professionals regardless of the zone in which they work. There is, therefore, no risk of a biased exploration of this knowledge, attitudes and practices based on the greater or lesser degree of exposure to the study subject. There will obviously be different levels of implication and sensitisation towards the subject which will be shown in the results of the study. With respect to the families, this geographical concentration will facilitate access to the communities although we are aware that there may be social or group conditioners which may influence in the perception of the problem on behalf of the interviewers and in their responses.

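### Professionals answer in whole teams and centres are expected to differ, but the tests and the logistic model state no handling of within-team correlation

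*Protocol article*

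**What the plan says.** Methods/design sets the frame: "The study will be carried out in the 25 Primary Healthcare Centres". The section on how providers are selected states: "The study includes all the professionals of the PHC teams, the Sexual and Reproductive Healthcare Programme and the Departments of Paediatrics and Gynaecology-Obstetrics". The departments meant are hospital ones. This is an attempted census of whole teams, with an expected response of about 75%.

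Data collection adds that "The questionnaires will be given and collected in a specific session in each PHC". On the questionnaire it says "It will only have a code indicative of the team to which the health professional belongs to obtain the rate of response from each centre". The response rate is the only use given for that code.

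The Analysis plan describes each item and then tests it against gender, age, professional category and centre or department, with tests chosen by type of data. It continues: "A multiple logistic regression model will be used to assess the characteristics of the professionals associated with correct identification of FGM". The threshold is p < 0.05. No random effect, GEE, robust variance or design effect is mentioned. Elsewhere, the sample-size section allows the main results to be stratified by participation rate if that proves necessary.

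The Discussion states that "the level of sensitisation for the problem of the study may vary greatly based on the demographic reality of each PHC". It then concludes that this cannot affect the results, because every professional is targeted whatever the zone.

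**The concern.** Colleagues in one centre serve the same population, see similar numbers of affected families and complete the form in the same session. If sensitisation differs strongly between centres, their answers are correlated. A test that ignores this has a standard error that is too small for any characteristic that differs mainly between teams rather than within them.

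Professional category is partly such a characteristic. Selection of healthcare providers places gynaecologists and midwives mainly in the sexual and reproductive health support programmes, and family physicians, paediatricians and social workers in the primary care teams. The earlier survey cited in the Background reported a contrast of this kind: 21% of reproductive-health personnel had met a case, against 7% of paediatricians and 5% of general medicine professionals.

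At stake is which characteristics are reported as associated with correct identification of FGM, and how far the findings carry beyond these centres.

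The Discussion's reasoning is the second half of the problem. Inviting everyone removes selection of professionals by zone. It does not make answers within a team independent.

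**Working it through.** **Inputs from the article.** 25 centres; all professionals invited; about 75% response; one session per centre; a team code on each form; p < 0.05. The article gives no sample size for the professionals, so there is no figure to reproduce. Its only sample size, 191, belongs to the family survey and has no bearing here.

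**Assumed inputs.** Respondents per team (m) and intraclass correlation (ICC) are not given. The ranges used are m = 20 to 40 and ICC = 0.02 to 0.10.

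**Step 1: a factor constant within teams.** Design effect DE = 1 + (m − 1) × ICC. The true standard error is √DE times the naive one. The true error of a nominal 5% two-sided test is 2 × [1 − Φ(1.96/√DE)].

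| m | ICC | DE | √DE | True error |
|---|---|---|---|---|
| 20 | 0.02 | 1 + 19 × 0.02 = 1.38 | 1.17 | 9.5% |
| 20 | 0.05 | 1 + 19 × 0.05 = 1.95 | 1.40 | 16% |
| 30 | 0.05 | 1 + 29 × 0.05 = 2.45 | 1.57 | 21% |
| 40 | 0.10 | 1 + 39 × 0.10 = 4.90 | 2.21 | 38% |

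The range is therefore about 10% to 38%.

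**Step 2: factors that vary within teams.** The formula in step 1 does not apply to these, so ordinary logistic regression was simulated: 25 centres, 2,000 runs per setting, no true effect of the covariate, ICC set on the logit scale. The even covariate is an individual characteristic spread evenly over centres. The partly clustered one has a covariate ICC of 0.1.

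| m | ICC | Even | Partly clustered | Constant within centre |
|---|---|---|---|---|
| 20 | 0.02 | 5.0% | 5.4% | 8.2% |
| 20 | 0.05 | 4.5% | 5.7% | 14.5% |
| 20 | 0.10 | 5.1% | 6.9% | 21.9% |
| 30 | 0.02 | 4.9% | 5.5% | 10.9% |
| 30 | 0.05 | 4.8% | 6.4% | 17.6% |
| 30 | 0.10 | 4.9% | 7.7% | 27.7% |

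The simulation error at 5% is √(0.05 × 0.95/2000) ≈ 0.5 percentage points, so the even column does not differ from 5%. The last column lies somewhat below the formula, partly because an ICC on the logit scale means a slightly smaller correlation between yes/no answers.

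**Step 3: the factors the plan names.**
- Gender and age vary within teams. Unless they happen to concentrate in some centres, they belong in the even column.
- Professional category is mixed within primary care teams but concentrated for gynaecologists and midwives. The partly clustered column is the nearest match.
- Centre is the cluster itself. Under the hypothesis that centres do not differ there is no between-centre variance, so that test is not inflated.
- Type of department, if compared as a group of teams, is constant within teams. Only there do the large figures apply.

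**The case against.** The strongest reply is that this is a condensed article. The bivariate tests are unnamed, and the model's covariates and variance estimator are not listed, so a full plan may already deal with clustering. That stands against saying that respondents are treated as independent. It does not remove the point, because the article takes up between-centre variation itself and dismisses it with an argument about who is targeted.

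A reader might infer three stronger claims that the article does not support:
- **All p-values are too small.** They are not. The named individual characteristics mostly vary within teams, where the error stays close to 5%.
- **Confidence intervals are too narrow.** None is planned for the professionals.
- **Centre is ignored, so it confounds category and age.** Centre or department is a planned bivariate factor, stratification by participation rate is foreseen, and nothing shows that centre is left out of the model.

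It can also be said that the study is an attempted census with mainly descriptive aims, so that clustering matters only for inference beyond these centres. This is right for the descriptive percentages. But the plan applies significance tests, and the Discussion looks to training needs among professionals nationally, so wider inference is intended. Finally, the fourth objective, on training needs, draws mainly on the knowledge results as a whole. The link from the model's p-values to training recommendations is therefore loose.

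**Conclusion.** The concern holds in a limited form. The article describes clustered data, expects centres to differ, collects the identifier needed, and states no method for within-team correlation in the professionals' tests or model. The ground on which the Discussion dismisses the matter answers a different question.

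For the named individual characteristics the effect is small: about 5% if evenly spread, and roughly 5% to 8% for a covariate ICC of 0.1 with 20 or 30 respondents per centre. An error of about 10% to 38% applies only to a factor constant within teams, such as type of department if it is compared. Every figure rests on assumed team sizes and ICCs. The direction is certain only for factors concentrated in teams. The change is worth making because it is cheap, not because the planned results would otherwise be unusable.

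**What to change.** 1. In the Analysis plan, state that the professionals' logistic model includes a random intercept for the team code, or uses GEE or a cluster-robust variance by team. Say which, since the first gives odds ratios within a team and the second gives population averages. With about 25 clusters, a small-sample correction to a robust variance is sensible.
2. Use cluster-adjusted versions of the bivariate tests for gender, age and professional category. If types of department are compared, treat the team as the unit of variation.
3. In Data collection, add this analysis as a second use of the team code.
4. In the Discussion, say that inviting all professionals deals with selection by zone but does not remove correlation within teams.

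The planned descriptive comparison of centres can stay. Replacing it with a variance component would be a matter of preference. No new data are needed. The cost is slightly more analysis work and some larger p-values, mainly for factors concentrated in teams.
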